## Abstract

**Background:**

The incidence of colorectal cancer among the middle-aged and elderly is gradually increasing in China. Colonoscopy is an effective method for the early diagnosis of colorectal cancer, and bowel preparation is one of many important factors affecting colonoscopy. Although there are many studies on intestinal cleansers, the results are not ideal. There is evidence that hemp seed oil has certain potential effects in intestinal cleansing, but prospective studies on this topic are still lacking.

**Methods:**

This is a randomized, double-blind, single-center clinical study. We randomly assigned 690 participants to groups each administered 3 L of polyethylene glycol (PEG), 30 mL of hemp seed oil and 2 L of PEG, or 30 mL of hempseed oil, 2 L of PEG, and 1000 mL of 5% sugar brine. The Boston Bowel Preparation Scale was considered the primary outcome measure. We evaluated the interval between consumption of bowel preparation and first bowel movement. Secondary indicators included the time of cecal intubation, detection rate of polyps and adenomas, willingness to repeat the same bowel preparation, whether the protocol was tolerated, and whether there were adverse reactions during bowel preparation and were evaluated after counting the total number of bowel movements.

**Discussion:**

This study aimed to test the hypothesis that hemp seed oil (30 mL) increases the quality of bowel preparation and reduces the amount of PEG. Previously, we found that its combination with 5% sugar brine can reduce the occurrence of adverse reactions.

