Therefore, we hypothesized that the oral administration of 30 mL hemp seed oil in stages could enhance the intestinal cleansing ability of PEG, decrease the dosage of PEG without any obvious adverse effects, and increase its acceptance. This trial aimed to determine the efficacy, safety, and tolerability of 2 L of PEG plus hemp seed oil in combination with 5% sugar brine for bowel preparation.

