### Objectives

This study aimed to investigate the potential of 30 mL of hemp seed oil in enhancing bowel cleansing. The study also evaluated the effect of reducing PEG by half by adding hemp seed oil and 5% sugar brine on reducing the adverse effects of bowel preparation and increasing the patients’ tolerance of PEG.

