### Study protocol

All subjects undergoing colonoscopy should start a no-pigment, low-residue, low-fiber diet 3 days before examination and fast at 18:00 the night before the examination. If hypoglycemia or other discomforts occur due to hunger on the same day, oral colorless vitamin drinks or candy bars can be taken to enhance tolerance. Moreover, to allay the participants’ fear of intestinal preparation, researchers should explain the purpose of colonoscopy, importance of adequate intestinal preparation, and potential adverse events that may occur during intestinal preparation.

Figure 2 depicts the drug use schemes of the 3 groups. The oral intestinal preparation process under the guidance of researchers in the 3 L of PEG group was as follows: one bag of PEG and 1 L of clear fluids was taken orally at 22:00 the day before the examination, the second bag was taken 4–6 h before the examination, and the third bag of PEG was taken half an hour later (Fig. 2A). As for the 30 mL of hemp seed oil and 2 L of the PEG group, patients orally took 15 mL of hemp seed oil in divided doses at 20:00 and 22:00 1 day before the examination, the first bag of PEG and 1 L of clear fluids 4–6 h before the examination, and the second bag of PEG half an hour later (Fig. 2B). Regarding the 30 mL of hemp seed oil, 2 L of PEG, and 5% sugar brine group, patients orally took 15 mL of hemp seed oil in divided doses at 20:00 and 22:00 1 day before the examination, the first bag of PEG and 1000 mL of 5% sugar brine 4–6 h before the examination, and another bag of PEG half an hour later (Fig. 2C). In the study, participants were free to drink clear fluids after the commencement of bowel preparation. The study schedule is shown in Fig. 3.

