#### Secondary outcomes

Adverse reactions that occur during bowel preparation are the secondary outcome indicators of the study. We evaluated the interval between taking bowel preparation and the first bowel movement, the total number of bowel movements completed, time of cecal intubation, detection rate of polyps and adenomas, willingness to repeat the same bowel preparation, whether the protocol is tolerated (0 points for no discomfort; 1 point for mild discomfort; 2 points for ability to tolerate; 3 points for not being able to tolerate), and adverse events.

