## Discussion

Colonoscopy can be used to visually diagnose intestinal diseases and reduce the incidence of colorectal cancer. The survey showed that the incidence of colorectal cancer in China increases with age [40]. Poor bowel preparation is an important factor that affects the failure of cecal intubation during colonoscopy and leads to a missed diagnosis of some polyps or lesions, which may warrant repeated colonoscopy [41]. There are many studies on modified bowel preparations; however, because of the existence of many adverse reactions or poor medical compliance and tolerance by patients, it is necessary to find safer and more effective bowel preparation methods [42–44]. Currently, many studies have demonstrated the laxative effect of hemp seed oil. However, there is no research on its use in bowel preparation, making it necessary to explore whether 30 mL of hemp seed oil can improve the bowel cleansing potential of PEG in bowel preparation.

We designed a randomized, double-blind, single-center clinical trial to investigate whether 30 mL of hemp seed oil can improve the potential of 2 L PEG for bowel preparation and whether a combination of 30 mL hemp seed oil and 5% sugar brine can reduce the required volume of PEG, as well as reduce the adverse reactions during bowel preparation.

The results of this trial will influence evidence-based decision-making for bowel preparation regimen prescriptions as it will be fundamental in providing reliable recommendations for bowel preparation regimens before colonoscopy.

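### The aims are about hemp seed oil itself, but the arms compare whole regimens: oil is aliased with removal of one PEG bag, so no planned contrast estimates its effect

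*Protocol article*

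**What the plan says.** Four places in the protocol article express an aim about the oil as an ingredient:

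- Abstract, Discussion: the hypothesis under test is that the oil "increases the quality of bowel preparation and reduces the amount of PEG".
- Introduction, last paragraph: the oil "could enhance the intestinal cleansing ability of PEG, decrease the dosage of PEG without any obvious adverse effects".
- Objectives: to "investigate the potential of 30 mL of hemp seed oil in enhancing bowel cleansing".
- Discussion: "whether 30 mL of hemp seed oil can improve the potential of 2 L PEG for bowel preparation". The natural comparator for this question is 2 L PEG without oil.

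Other text is at regimen level. Trial design and setting describes a three-arm non-inferiority study. The Introduction closes by saying the trial will assess efficacy, safety and tolerability of the 2 L PEG, oil and brine combination.

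The arms are set out under Recruitment, randomization, and blinding and under Study protocol. In A, the first PEG bag "was taken orally at 22:00 the day before the examination"; the second follows 4–6 h before the examination and the third half an hour after that. B has 15 mL of oil at 20:00 and again at 22:00 the evening before, then one PEG bag 4–6 h before the examination and one half an hour later. C is B with 1000 mL of 5% sugar brine in place of 1 L of clear fluids. Statistical analysis compares the main results by chi-square test.

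**The concern.** To learn what an ingredient does, some pair of arms must differ in that ingredient and nothing else. Here every arm with oil also lacks A's evening PEG bag, and the only arm without oil has it. If B or C turns out similar to A, which is what a non-inferiority trial sets out to show, two explanations fit equally well: the oil made up for the missing bag, or the bag was not needed and 2 L PEG would have done as well alone. If B turns out worse than A, the oil may still have helped, only by less than the bag.

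At stake is the conclusion, not the validity of the comparison. The Discussion expects the results to support recommendations on preparation regimens. A conclusion worded to match the stated aims would credit the oil with an effect that the arms cannot separate from the change in PEG.

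The second half of the hypothesis, less PEG, is fixed by allocation and is not an outcome. What can be tested is whether cleansing holds up when less PEG is given.

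**Working it through.** **Step 1. Arm contents (from Study protocol).**

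| Arm | Evening oil | PEG bag at 22:00 | Two examination-side PEG bags | Brine in place of clear fluids |
|---|---|---|---|---|
| A | no | yes | yes | no |
| B | yes | no | yes | no |
| C | yes | no | yes | yes |

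The two examination-side bags have the same window and the same half-hour gap in all arms. The change in PEG volume (3 bags to 2) and the change in PEG timing are therefore one difference: A's 22:00 bag. The article names 1 L of clear fluids with the first bag of A and of B. If that is a separate litre, its shift from evening to examination side belongs to the same bundle.

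**Step 2. What each contrast estimates.** Let m be the success rate with the two examination-side bags and clear fluids alone, e the effect of adding the 22:00 bag (with any fluid tied to it), o the effect of the oil and s the effect of brine in place of clear fluids. Assume, in the design's favour, that effects add:

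- A = m + e
- B = m + o
- C = m + o + s

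Then:

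- B − A = o − e
- C − A = o − e + s
- C − B = s

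**Step 3. Can any combination recover o?** Take weights a, b, c on A, B, C. The sum is (a + b + c)m + a·e + (b + c)o + c·s. To leave o alone requires a = 0 (removes e), c = 0 (removes s) and a + b + c = 0 (removes m). These force b = 0, so the coefficient of o is 0 too. No combination works: 0 of 3 pairwise contrasts, and no pooled contrast such as B and C against A. Sample size does not enter, so the planned 690 (690 / 3 = 230 per arm) neither causes nor cures this.

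**Step 4. Size of the ambiguity.** Sample size gives 80% as the success rate with 3 L PEG. The documents give no rate for 2 L PEG alone, so m is an assumed range. With A = 80%, the oil effect is o = B − m:

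| Assumed m | o if B = 80% (equal to A) | o if B = 75% (below A) |
|---|---|---|
| 65% | 80 − 65 = 15 points | 75 − 65 = 10 points |
| 70% | 10 points | 5 points |
| 75% | 5 points | 0 points |
| 80% | 0 points | −5 points |

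Each column is one trial result. Equality of A and B fits an oil effect anywhere from 0 to 15 points over this range.

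**Step 5. If B beats A.** With A = 80% and B = 85% (the rates in Sample size), o = 5 + e points. If the extra evening bag cannot harm (e ≥ 0), o is at least 5 points. That would be suggestive, but it rests on an assumption about e that the trial does not test. Nor is such a result likely at these rates. Power (two-sided 0.05, 230 per arm) = Φ[(0.05 − 1.96·√(2·0.825·0.175/230)) / √((0.80·0.20 + 0.85·0.15)/230)] = Φ[(0.05 − 0.0694)/0.0354] = Φ(−0.55) = 0.29.

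**Step 6. Time to first movement.** Secondary outcomes says "We evaluated the interval between taking bowel preparation and the first bowel movement". Intake begins with oil at 20:00 in B and C and with PEG at 22:00 in A, while PEG in B and C begins only 4–6 h before the examination. Counting from first intake and counting from first PEG are thus different quantities in B and C and the same quantity in A. The article does not say which is meant.

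**The case against.** The strongest reply is that comparing a reduced-volume regimen plus an adjunct with a standard regimen is a legitimate design, and that the article says as much: it calls the trial non-inferiority and ends its Introduction with a regimen aim. B versus A is a clean substitution contrast, evening oil for one evening PEG bag, and speaks directly to whether the oil regimen can spare 1 L of PEG. Randomization protects that comparison. All of this stands, and it is why the point concerns the wording of aims and conclusions and not the arms.

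It does not dispose of the point. The same article also states oil-specific aims in four places, and the Discussion's question about improving 2 L PEG has no comparator among the arms. That the article condenses a fuller protocol does not help: arms, volumes and clock times are all given, and nothing is alleged to be omitted.

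Three stronger readings are tempting and are not supported:

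- A reader might count oil, PEG volume and PEG timing as three separate confounded differences between A and B. Volume and timing are one difference, because the two examination-side bags match.
- A reader might infer that the sponsor promises to prove an oil effect. The text speaks of testing a hypothesis and investigating a potential; how the results will be reported is not known.
- A reader might infer that the interval to first movement is not comparable with A and should lose its test. The start point is undefined in a condensed article and may be defined in the full protocol. The oil is called an adjuvant, so first PEG could be meant, and every arm has that start. Dropping the P value would be a preference.

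**Conclusion.** The concern holds in a limited form. Aims about the oil's own effect cannot be met: oil is completely aliased with removal of one PEG bag, and this follows from the arm definitions alone, whatever the sample size or test. Similarity of B or C to A would not show that the oil contributed anything. The regimen comparisons and the brine contrast (C versus B, apart from the clear fluids that participants may drink freely) are unaffected.

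The conclusion needs no assumed rate. The additive model in the working is generous to the design; interactions between oil, PEG and brine would only add unknowns. The 65–80% range for 2 L PEG alone is an assumption used to illustrate size. This is worth correcting before unblinding, but it is not a flaw in the conduct or validity of the trial.

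**What to change.** 1. Reconcile the oil-specific sentences in the Abstract, Introduction, Objectives and Discussion with the non-inferiority design. Restate the hypothesis, objectives and planned conclusion at regimen level: is regimen B (or C) non-inferior to 3 L PEG?
2. State that the trial does not estimate the effect of hemp seed oil itself. Present the lower PEG volume as a feature of the regimens and not as a result.
3. Name C versus B as the only single-component contrast: brine against clear fluids, with freely taken fluids noted as a limit.
4. At most, for the interval to first bowel movement, report it both from first intake and from first PEG and say which is which.

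No arm, dose, schedule, sample size or primary test changes on this account. The route is the one under Protocol amendments: ethics committee review and an update of the registry entry. The cost is a narrower claim, with no statement that the oil as such improves cleansing.

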**Trial registration:**

Chinese Clinical Trial Registry ChiCTR2200057626. Prospectively registered on March 15, 2022

**Supplementary Information:**

The online version contains supplementary material available at 10.1186/s13063-022-07059-1.

## Introduction

Colorectal cancer is a common malignant tumor of the digestive system. According to a report of the cancer survey, colorectal cancer ranks in the top three in new cases and deaths in both men and women, making it one of the most life-threatening cancers among Chinese patients [1, 2]. The progression of colorectal adenomas to cancer may take up to 10 years, and the incidence increases with age [3–6]. Moreover, the risk of mortality from colorectal cancer has been reported to decrease by 53% in patients who underwent endoscopic adenoma resection [7–10]. Many factors affect the quality of colonoscopy, of which bowel preparation is an essential factor. Inadequate bowel preparation can reduce the adenoma detection rate, prolong the duration of colonoscopy, and increase the risk of examination [11–13].

Currently, polyethylene glycol (PEG) is still the first choice for clinical intestinal preparation. Due to its poor taste, the need to drink a lot of water and adverse events, such as nausea and vomiting, patients have reduced tolerance and medical compliance for PEG [14, 15]. According to a survey, the incidence of constipation is higher among middle-aged and elderly patients than among younger patients owing to factors such as a decline in intestinal function and dietary habits, affecting the quality of bowel preparation [16, 17]. Recently, many clinical studies on bowel preparation are being conducted with the aim of improving the quality of bowel preparation and patients’ tolerance. Examples of such studies include those on the application of ascorbic acid, senna, and sodium phosphatases [18–21]. However, many trials have not achieved the expected results pertaining to bowel preparation. Therefore, improving the quality of bowel preparation and reducing the amount of PEG is still a problem that needs to be solved.

Hemp seed has been used as food and medicine in China for more than 3000 years, and it is listed as a Chinese medicinal material of the same origin as medicine and food by the National Health Commission [22, 23]. It can regulate constipation, improve immunity, and treat diseases of the gastrointestinal tract. There are many mechanisms through which hemp seed regulates constipation, including regulating intestinal flora, promoting the growth of probiotics to improve intestinal function, and regulating ion channels on the surface of intestinal epithelial cells, which play a role in regulating constipation [24–26]. Currently, there are many clinical studies on Maziren pills formulated with hemp seed, which have found that it has a good curative effect on constipation in elderly patients [27–29]. Hemp seed oil is a highly nutritious vegetable oil obtained by pressing or leaching hemp seed. It is rich in unsaturated fatty acids, amino acids, vitamin E, alkaloids, and other components with high nutritional value [30]. The unsaturated fatty acids present in hemp seed help regulate blood lipids and the immune system [31, 32]. Despite hemp seed oil having high edible and medicinal value, it contains delta-9-tetrahydrocannabinol acid (Δ9-THCA). At certain concentrations in the body, it may produce symptoms such as abdominal distension, sweating, and vomiting, which are the main adverse reactions [33–35]. According to the Chinese dietary nutrition guidelines, the recommended daily intake of the edible oil is 25–30 g. This study used 30 mL of hemp seed oil that meets the edible standard as an adjuvant drug for bowel preparation.

Hemp seed oil has a laxative effect; thus, it was combined with PEG to reduce the amount of PEG used in this study. Moreover, due to the poor taste of PEG and some adverse events caused by insufficient caloric intake during intestinal preparation, patients’ bowel preparation can be poor. Therefore, 5% sugar brine (5% glucose and 0.9% sodium chloride) was added to improve the taste of PEG and replenish energy and electrolytes. Additionally, 5% sugar brine is isotonic, can prevent dehydration caused by catharsis, and keep the intestinal mucosal cells in an isotonic state. When the fluid flow in the intestine exceeds a certain flow rate, the emptying of intestinal contents can be accelerated, which can assist in intestinal cleansing.

Therefore, we hypothesized that the oral administration of 30 mL hemp seed oil in stages could enhance the intestinal cleansing ability of PEG, decrease the dosage of PEG without any obvious adverse effects, and increase its acceptance. This trial aimed to determine the efficacy, safety, and tolerability of 2 L of PEG plus hemp seed oil in combination with 5% sugar brine for bowel preparation.

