### Sample size

We calculated the expected sample size based on the preliminary extrapolation of the results of bowel preparation before the study began. According to the results of previous studies, when using 3 L PEG for bowel preparation, the qualified rate of bowel preparation was 80%. PEG was accepted as the standard preparation, and the aforementioned percentage was taken as a reference [18, 20, 37, 38]. Assuming the qualified rate of bowel preparation in this study is 85%, the alpha level was set to 0.05. When a sample size of 690 was calculated, a 5% difference between the three groups could be determined.

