### Statistical analysis

In this study, we will adopt intent-to-treat and per-protocol methods to analyze all data. The basic information of patients is expressed by mean, median, and standard deviation. The chi-square test will be used to compare the categorical variables in the basic data of patients. In two independent samples, the Mann–Whitney *U*-test and Student’s test will be used for the comparison of continuous variables; the chi-square test will be used for the comparison of the main results; secondary outcomes will be compared using the chi-square test for categorical variables and Student’s *t*-test for continuous variables. All statistical analyses will be conducted with the 2-tailed test, and *P* < 0.05 will be considered statistically significant. We will make every attempt to collect complete information for all participants and avoid missing data. If necessary, missing data will be handled using multiple imputation. As no formal stopping rules have been specified for this study, no formal interim analyses are planned, and hence, no statistical testing will take place until the final analysis. All data were analyzed using SPSS 26 (SPSS Inc., an IBM Company, Chicago, IL).

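### A non-significant chi-square on adverse reactions cannot support the hypothesised absence of obvious harm; report risk differences with 95% confidence intervals beside it

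*Protocol article*

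**What the plan says.** The last paragraph of the Introduction in the protocol article makes lack of added harm part of the hypothesis: the oil is expected to "decrease the dosage of PEG without any obvious adverse effects, and increase its acceptance". The next sentence lists safety among the aims. The Introduction also gives a reason to look for harm. It says of a cannabinoid constituent of the oil that, at certain concentrations, "it may produce symptoms such as abdominal distension, sweating, and vomiting, which are the main adverse reactions".

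The Objectives section frames the adverse-effect question differently, as the effect of the modified regimen "on reducing the adverse effects of bowel preparation". Under Secondary outcomes, "Adverse reactions that occur during bowel preparation are the secondary outcome indicators of the study".

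The Statistical analysis section says that "secondary outcomes will be compared using the chi-square test for categorical variables" and that "All statistical analyses will be conducted with the 2-tailed test", with P < 0.05 as the threshold. It mentions no risk difference, confidence interval or upper limit for adverse reactions. No section gives an expected rate for any reaction in any arm.

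**The concern.** A test of no difference can show that two arms differ. Failing to reject does not show that they are alike. A finding of fewer reactions can therefore come out of the stated test, but a finding of no added harm cannot. If no reduction is shown, a report that has only the P-value leaves the reader unable to tell a small excess ruled out from a sizeable excess missed.

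This matters because the Discussion expects the results to inform prescribing of bowel-preparation regimens, and because the regimens under test add an oral product for which the article itself names possible reactions. The point concerns adverse reactions only. It does not concern the primary comparison of bowel-preparation quality.

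**Working it through.** **Inputs from the article**
- Total 690 (Sample size), allocated 1:1:1 (Recruitment, randomization, and blinding): 690 / 3 = 230 per arm, all taken as evaluable.
- Two-sided alpha of 0.05: "the alpha level was set to 0.05" (Sample size) and the two-tailed rule in Statistical analysis.

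**Inputs assumed**
- Reaction rate on PEG alone: the article gives none, so a range from 1% to 30% is used.
- Excess of 5 percentage points in an oil arm: an illustration only. The 5% in the article ("When a sample size of 690 was calculated, a 5% difference between the three groups could be determined") belongs to bowel-preparation quality.

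**The plan's own figure.** The 690 was set on bowel-preparation quality, not on adverse reactions. It is approximately reproduced if the 5 points are read as a non-inferiority margin with 80% power and one-sided alpha 0.025; the article states neither that reading nor the power.

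n = (1.96 + 0.8416)² × (0.80×0.20 + 0.85×0.15) / (0.05 + 0.05)² = 7.849 × 0.2875 / 0.01 = 225.7, so 226 per arm and 678 in total.

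For the present point only the 230 per arm matters.

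**Power of the stated test, one oil arm against arm A.** With control rate p, oil-arm rate q = p + 0.05 and pooled rate m = (p + q)/2:

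- SE0 = √(2m(1 − m)/230)
- SE1 = √((p(1 − p) + q(1 − q))/230)
- power ≈ Φ((0.05 − 1.96 × SE0)/SE1)

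At 10% vs 15%, SE0 = 0.03084 and SE1 = 0.03075, so z = (0.05 − 0.06045)/0.03075 = −0.340 and power is 0.367. Exact binomial enumeration of the uncorrected Pearson chi-square, counting rejections in the direction of harm, gives 0.371.

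| Control vs oil arm | Approximate power | Exact power | Chance of missing the excess (exact) |
|---|---|---|---|
| 1% vs 6% | 83% | 88% | 12% |
| 2% vs 7% | 74% | 76% | 24% |
| 5% vs 10% | 53% | 53% | 47% |
| 6% vs 11% | 49% | 49% | 51% |
| 10% vs 15% | 37% | 37% | 63% |
| 20% vs 25% | 25% | 25% | 75% |
| 30% vs 35% | 21% | 21% | 79% |

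Approximate power crosses 50% at a control rate of about 5.7%. Pooling both oil arms (460) against PEG moves the crossing to about 8%, with 44% power at 10% and 31% at 20% by the approximate formula.

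**Precision.** The 95% half-width for a risk difference at a common rate p is 1.96 × √(2p(1 − p)/230): 4.0 points at 5%, 5.5 at 10% and 7.3 at 20%.

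**What the interval adds.** Suppose 23 of 230 patients (10.0%) react in arm A and 34 of 230 (14.8%) in arm B. The difference is 4.8 points, the pooled rate is 57/460 = 0.124, SE0 = 0.0307, z = 0.0478/0.0307 = 1.56 and P = 0.12. The stated test reports no significant difference. The simple 95% interval is 4.8 ± 1.96 × 3.06, that is −1.2 to 10.8 points (Newcombe: −1.3 to 10.9). An excess of more than 10 points has not been excluded, and the P-value alone does not show that.

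**The case against.** The strongest reply is that the stated test fits the stated objective. The Objectives section and the Discussion speak of reducing adverse reactions. A two-sided difference test answers that question and can also detect harm. The hypothesis wording is informal and puts no number on what would count as obvious. This stands in part: the test is right for the reduction aim, and nothing here argues for removing it. It does not meet the no-added-harm wording, which the article presents as part of the hypothesis next to a safety aim.

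A second reply is that confidence intervals and safety tables are commonly left to a full protocol or analysis plan. That is fair, and it is why a missing safety margin is not raised as a defect. What remains is that the article itself states both the hypothesis and the test, and the test cannot deliver that part of the hypothesis.

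Three stronger readings are tempting, and the article does not support them:
- A reader might infer that a non-significant result will be declared safe. No section says so.
- A reader might infer that a 5-point excess would usually be missed. That holds only from a control rate of about 6% upward; at 1% to 2% such an excess is detected 76% to 88% of the time. Nausea and vomiting are named as known problems with PEG, so some reactions may be common, but no rate is given.
- A reader might infer that the article says the oil at the study amount causes these symptoms. It ties them to a constituent at certain concentrations, and it does not list electrolyte imbalance among them; that comes from the general recording list under Safety assessments.

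**Conclusion.** The concern holds in a limited form. The chi-square is adequate for testing a reduction in adverse reactions, but its non-significance is not evidence for the no-added-harm part of the hypothesis. The gap is material for reactions that are not rare: with 230 evaluable patients per arm and a 5-point excess taken as illustration, power is under 50% from a control rate of about 6%. For rare reactions the test does reasonably well against an excess of that size. These figures depend on assumed rates and an assumed excess, because the article supplies neither. The conclusion about what the test can and cannot show does not depend on them. This is a matter of reporting and interpretation; it does not call for a larger trial.

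**What to change.** In Statistical analysis, add for the recorded adverse reactions, at least vomiting, abdominal distension or bloating, and sweating:

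1. The risk differences B − A and C − A, each with a two-sided 95% confidence interval (Newcombe or Miettinen–Nurminen), reported beside the chi-square.
2. A sentence that any statement about absence of obvious adverse effects will rest on the upper limit, reported as the largest excess the data do not exclude.
3. A sentence that P ≥ 0.05 will not be read as absence of harm.

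A formal tolerable excess is optional. If the investigators want one, they should set it before unblinding.

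The cost is some wording and one extra table from data already on the case report form, with no additional patients. The drawback is a weaker safety statement for common reactions. With equal true rates of 10%, the chance that the upper limit falls below 5 points is about Φ(0.05/√(2 × 0.10 × 0.90/230) − 1.96) = Φ(−0.17) = 43%. The report will therefore often have to say that an excess of several points is not excluded, even if there is none.
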